### **3.2 Participant Withdrawal, Removal, or Termination**

#### **3.2.1 Criteria for Participant Withdrawals**

- (1) The patients developed disease progression and could not benefit from further treatment determined by the investigators;
- (2) The patients experienced the AEs without tolerance and alleviation;
- (3) Subjects who experienced SAEs and were not suitable for further study;
- (4) Patients who did not meet the eligibility criteria following the additional review;
- (5) The serious protocol deviation or violation affected the evaluation of safety and efficacy;
- (6) Patients who withdrew consent;
- (7) Patients with failure to follow up for any reason.

#### **3.2.2 Handling of Participant Withdrawals**

Investigators should clearly collect the reason and time of withdrawal, conduct corresponding observation and evaluation of the withdrawn subjects, complete the evaluation content when withdrawing from the study as specified in the study plan, fill in the corresponding original records, and describe the reasons for withdrawal. Subjects who discontinue the study should continue to be

followed for AEs. If possible, these subjects should continue to follow up AEs until it recovers to the baseline level or the investigator believes that follow-up observation is unnecessary.

During the study period, all subjects who received the drug but did not complete the relevant study content of the protocol should have their last examination results transferred to the final result. Subjects who did not follow up as required and evidence of contact should be recorded in the corresponding original records and electronic data collections (EDCs; such as time and date of telephone contact, mailing receipt of registered mail, etc.) and properly preserved.

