## 9. Efficacy Evaluation

Since similar drugs of TQB2450 induced pseudo-progression in the clinical administration, the efficacy evaluation will be assessed by RECIST v1.1 and further confirmed by iRECIST criteria. That is, patients identified as having disease progression as per RECIST v1.1 will be confirmed by iRECIST to determine further treatment.

Efficacy will be assessed every 2 cycles from cycle 1 day 1 until the radiologically confirmed disease progression. The frequency of radiographic assessments is independent of dose delays and/or dose interruptions. For subjects who discontinue the study drug for reasons other than disease progression, the tumor assessment will still be conducted every 2 cycles until starting a new antitumor therapy, disease progression, withdrawal of consent, or death, whichever occurs first.

The methods of radiographic assessment (CT or MRI) will be determined by the investigator. However, the assessment methods, machines, and technical parameters should be consistent throughout the study period. Contrast media is required for subjects without contraindications. For subjects who had received a radiographic assessment within 14 days before the first dose using the same procedure in the same center, the radiographic assessment could be used as the baseline data in this trial. The baseline tumor assessment should include enhanced CT or MRI of the chest, abdomen, and pelvis (except for subjects with an allergy to contrast media). During the screening period, a cranial plain scan plus enhanced MRI, and bone scan is required for all subjects. However, for subjects without bone metastases, whether the bone scan is performed will be decided by the investigator according to the symptoms. All suspected lesions will be evaluated by imaging. For subjects with bone metastases, the lesions will be monitored using a bone scan. If there is no exacerbation of clinical symptoms in these subjects, re-examination is not required at each visit for tumor assessment; otherwise, a timely re-examination is necessary. An unplanned tumor evaluation should be performed for subjects with suspected disease progression before the next planned evaluation. The radiographic assessment will only be conducted for lesions, but suspected lesions will also be evaluated by imaging.

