### **13.4 Efficacy Analysis**

#### **13.4.1 Analysis of Primary Efficacy Endpoints**

##### **➤ PFS**

The median PFS will be estimated using the Kaplan-Meier method and presented with the Kaplan-Meier curve.

The comparison of PFS between intervention arms will be performed using a stratified log-rank test. The HR and the corresponding 95%CI will also be provided based on a Cox proportional hazard model, using ECOG PS (0 vs. 1), brain metastases (yes vs. no), and liver metastases (yes vs. no) as concomitant variables. The results of the unstratified log-rank test and results of the Cox proportional hazard model without covariates adjustment will also be provided.

Subgroup analysis of PFS will be performed based on stratification factors.

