##### **➤ DOR**

The median DOR will be estimated using the Kaplan-Meier method and presented with the Kaplan-

Meier curve. The comparison of DOR between intervention arms will be performed using a stratified log-rank test. DOR will be only analyzed in responders.

➤ **DCR**

The number and percentage of subjects with the disease control (PR, CR, or SD) will be presented. The DCR and corresponding 95%CI will be summarized using F-distribution by binomial probabilities. The difference in DCR between intervention arms will be compared by the stratified CMH test. Stratification factors as items specified in section 4.3.

➤ **6-month and 12-month PFS rates**

The PFS rate and the corresponding 95%CI for each intervention arm will be estimated using the Kaplan-Meier method and compared with Fisher's Exact Test.

➤ **12-month and 18-month OS rates**

The OS rate and the corresponding 95%CI for each intervention arm will be estimated using the Kaplan-Meier method and compared with Fisher's Exact Test.

➤ **HRQOL**

HRQOL will be summarized by descriptive statistics. The changes of each item from baseline at each scheduled visit will be summarized by mean, SD, median, minimum, and maximum within each intervention arm. The grade of each item will be presented by the number and percentage and compared with the Wilcoxon rank sum test between intervention arms.

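### Section 3.2.2 carries the last examination forward for dosed non-completers, which conflicts with the time-to-event methods of section 13 and exposes the Fisher landmark tests and HRQOL by visit

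*Protocol*

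**What the plan says.** Section 3.2.2 of the protocol deals with withdrawn participants. It covers "all subjects who received the drug but did not complete the relevant study content of the protocol" and says that they "should have their last examination results transferred to the final result". It names no variable and makes no exception. Section 13 neither repeats nor withdraws the rule.

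Section 13.4.1 treats both primary endpoints as time-to-event: "The median PFS will be estimated using the Kaplan-Meier method and presented with the Kaplan-Meier curve". It adds a stratified log-rank test and a Cox model, and OS is handled the same way.

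Section 13.4.2 mixes two methods for the landmark rates: "The PFS rate and the corresponding 95%CI for each intervention arm will be estimated using the Kaplan-Meier method and compared with Fisher's Exact Test". The 12- and 18-month OS rates get the same treatment. For HRQOL: "The changes of each item from baseline at each scheduled visit will be summarized by mean, SD, median, minimum, and maximum", with a Wilcoxon rank sum test on item grades. Section 13.2.2 sets a two-sided 0.05 level for secondary efficacy endpoints.

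Three other places bear on who is affected. Section 3.2.1 lists progression as a withdrawal reason: "The patients developed disease progression and could not benefit from further treatment determined by the investigators". Section 9 keeps scanning patients who stop drug without progression: "the tumor assessment will still be conducted every 2 cycles until starting a new antitumor therapy, disease progression, withdrawal of consent, or death". The post-treatment follow-up in section 7 contacts all subjects every 8 weeks until death.

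**The concern.** A time-to-event analysis has no final result to fill in. A patient who leaves without an event contributes time up to the last adequate assessment and is then censored. A carry-forward instruction does not fit that framework, and the protocol does not say where it applies.

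It could take effect in two places.

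- **Landmark comparisons.** The rates are Kaplan-Meier estimates, but Fisher's exact test works on counts. A patient censored before month 6 or 12 has no yes/no status, so the analyst must assign one. The only rule the protocol offers is section 3.2.2, which makes that patient event-free. The same patient is then censored in the estimate and a success in the test.
- **HRQOL by visit.** An earlier questionnaire score could be copied into later scheduled visits, possibly past progression or death.

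Both are listed as secondary endpoints in section 3.6. At stake are P values for the landmark rates that do not correspond to the reported rates, and HRQOL summaries partly built from copied values.

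**Working it through.** **1. Planning inputs (section 4.1).** PFS hazards are 0.1733 per month in control and 0.1040 in arm 1. Accrual is 12 months, follow-up 18 months, and dropout 10% with no time attached.

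**2. Reproducing the plan's own figure.** With uniform accrual, P(event) = 1 − [exp(−18h) − exp(−30h)]/(12h). This gives 0.9814 in control and 0.9121 in arm 1. The mean of the two times 174 is 164.7 events, against the stated 165. The hazards are therefore used as the plan uses them. The plan expects an observed PFS event in 165/174 = 94.8% of analysed patients.

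**3. True 12-month PFS.** exp(−12h) gives exp(−2.080) = 12.5% in control and exp(−1.248) = 28.7% in arm 1, a difference of 16.2 points. Kaplan-Meier with non-informative censoring estimates these without bias.

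**4. Proportion counted event-free if section 3.2.2 feeds the Fisher count.** Assume exponential dropout at rate d, with the last status carried forward:

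proportion = exp(−(h+d)T) + [d/(h+d)] × [1 − exp(−(h+d)T)], T = 12.

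The first term is patients still followed and event-free; the second is patients lost event-free.

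- 10% by month 12: d = −ln(0.9)/12 = 0.00878. Control: 0.1125 + 0.0428 = 15.5%. Arm 1: 0.2584 + 0.0577 = 31.6%.
- 20% by month 12: d = −ln(0.8)/12 = 0.0186. Control: 0.1000 + 0.0872 = 18.7%. Arm 1: 0.2297 + 0.1168 = 34.7%.

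| Assumed dropout by month 12 | Control | Arm 1 | Difference (points) |
|---|---|---|---|
| None (true rate) | 12.5% | 28.7% | 16.2 |
| 10% in both arms | 15.5% | 31.6% | 16.1 |
| 20% in both arms | 18.7% | 34.7% | 16.0 |
| 10% control, 20% arm 1 | 15.5% | 34.7% | about 19 |
| 20% control, 10% arm 1 | 18.7% | 31.6% | about 13 |

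With 738/3 = 246 patients per arm, the 10% case reclassifies about 0.030 × 246 ≈ 7 patients in each arm.

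**5. Sensitivity to what 10% dropout means.** Suppose instead that 10% of each arm eventually leaves before progression, so d = 0.1h/0.9. The monthly dropout rate is then higher in control (0.0193) than in arm 1 (0.0116). The 12-month proportions become 18.9% and 32.5%, a difference of 13.6 points. At 6 months they are 38.3% against a true 35.4% in control, and 55.0% against 53.6% in arm 1. Over 5% to 20% dropout defined this way, the 12-month excess runs from 3.1 to 13.5 points in control and from 1.8 to 8.1 in arm 1.

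**6. HRQOL.** The protocol gives no means, standard deviations or missing rates, so nothing can be computed.

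**The case against.** The best defence is context. The sentence stands in an operational section on withdrawal records and is followed by instructions on documenting contact attempts. It may only mean that the last examination is entered as the final visit. No passage says that carried-forward status feeds the Fisher count; that link is inferred from two sections that do not refer to each other. This is a fair reading, and it is why limiting the sentence to record keeping is an acceptable fix. But as written the rule is unqualified, and Fisher's test needs a status that no other sentence supplies.

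A reader might infer more than the documents support:

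- **That the rule covers every non-completer and that most patients stop early.** It covers dosed subjects only. Treatment has no fixed length, planned dropout is 10%, and Table S3 of the supplement reports discontinuation for treatment-emergent adverse events in 19.9%, 15.2% and 10.6% of the three arms.
- **That progression-free status is overstated across the board.** Patients who withdraw for progression have progression as their last result, and it carries forward as progression. Scans continue after drug is stopped for other reasons, so only patients truly lost, withdrawing consent or starting new therapy while progression-free are exposed.
- **That the published 12-month PFS would become 15.5%.** The reported rates are Kaplan-Meier estimates. Only the count behind the P value could change.
- **That OS is equally exposed.** Survival is followed until death, and an examination result is not vital status, so the OS exposure is smaller.
- **That HRQOL would look falsely stable.** A questionnaire is scheduled at end of treatment, so the last score may already be low. Section 11 also calls HRQOL exploratory, although section 3.6 lists quality of life as secondary.

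One could also say that censoring rules belong in a statistical analysis plan, which is not shown. That holds for an omission. Here the protocol states a rule, and the rule conflicts with its own methods.

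**Conclusion.** The point holds in a limited form. Section 3.2.2 contains an unrestricted carry-forward instruction that contradicts the time-to-event methods of section 13. The primary PFS and OS tests and the reported landmark rates are untouched.

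The landmark PFS comparisons, and to a lesser degree the landmark OS comparisons, would rest on proportions biased upward if the rule were followed. The 12-month PFS excess is about 3 points per arm under 10% dropout by month 12 and about 6 points under 20%. The comparison between arms barely changes when monthly dropout rates are equal, and can move either way by about 3 points when they differ as in the table. These figures assume exponential, non-informative dropout and literal use of section 3.2.2 for the Fisher count; the size depends on how dropout is defined. For HRQOL the risk is real, but its direction and size are unknown.

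The mismatch between a Kaplan-Meier estimate and a Fisher test exists even without section 3.2.2. The carry-forward sentence settles it in a biased way. The change is worth making because it affects significance-tested secondary endpoints and is cheap.

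**What to change.** 1. Delete the carry-forward sentence in section 3.2.2, or restrict it to recording the date and findings of the last visit, with no role in analysis.
2. State that non-completers without an event are censored at the last adequate tumour assessment for PFS and at the last date known alive for OS.
3. In section 13.4.2, replace Fisher's exact test for the 6- and 12-month PFS and 12- and 18-month OS rates with a comparison of the Kaplan-Meier estimates using Greenwood variance, so that estimate and test treat each patient alike.
4. State that HRQOL is summarised on observed visits without carry-forward. A repeated-measures model is an option, not a requirement.

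The cost is a wording change and standard programming. No data collection, sample size or primary analysis changes.

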### **3.3 Criteria of Participant Removal**

- (1) Patients with chemotherapy, surgery, or other study drugs beyond the protocol during the trial;
- (2) Patients who failed to meet the inclusion criteria were mistakenly included.

### **3.4 Criteria of Termination**

- (1) The researchers found severe safety problems based on the decisions of investigators;
- (2) Withdrawal of the trial by the administrative department;
- (3) Termination by the sponsors.

### **3.5 Criteria of Continuous Treatment after PCI at the Maintenance Stage**

Brain metastases have been found in >50% of patients with SCLC. Studies showed that PCI could reduce the risks of brain metastases in SCLC patients. The randomized controlled EORTC study evaluated the differences in 286 ES-SCLC patients receiving or not PCI following response to initial chemotherapy. Compared with the control group, the symptoms of brain metastases were alleviated (14.6% vs. 40.4%) and the 1-year survival rate increased (27.1% vs. 13.3%) in the PCI group. In a randomized phase 3 study of evaluation of PCI in ES-SCLC conducted in Japan, although PCI reduced the risks of brain metastases (48% vs. 69%;  $P < 0.0001$ ), there was no overall survival benefit (11.6 months vs. 13.7 months;  $P = 0.094$ ). Therefore, PCI was recommended with caution for patients with ES-SCLC. The Chinese Society of Clinical Oncology (CSCO) Guidelines 2019 for the Diagnosis and Treatment of Primary Lung Cancer suggested that PCI should be started about 3 weeks after chemoradiotherapy. Brain-enhanced MRI should be performed before PCI, and PCI could be conducted without brain metastases. The dose of PCI was 25 Gy in 10 fractions over 2 weeks.

During maintenance therapy, patients are allowed to receive PCI, but not radical TR. The maintenance therapy after the PCI is conducted unless meeting the following criteria:

- Subjects within 28 days after completing required tests and assessments in the screening period still meet all inclusion criteria, but did not meet exclusion criteria (except the first-line therapy);
- Subjects do not receive antitumor treatments other than study therapy and PCI;
- PCI with drug-eluting stents for 2 weeks;
- The review and approval by the principal investigator.

If subjects continue to receive the maintenance therapy after PCI, subsequent follow-up should be

performed according to protocol until meeting the criteria for termination.

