| NSE       | Neural specific enolase                                                  |
| NCI-CTCAE | National Cancer Institute Common Terminology Criteria for Adverse Events |
| ORR       | Overall response rate                                                    |
| OS        | Overall survival                                                         |
| PT        | Prothrombin time                                                         |
| PCI       | Prophylactic cranial irradiation                                         |
| PFS       | Progression-free survival                                                |

|        |                                              |
|--------|----------------------------------------------|
| PLT    | Platelets                                    |
| PD     | Progressive disease                          |
| PD-1   | Programmed cell death protein 1              |
| PD-L1  | Programmed death ligand 1                    |
| PPS    | Per-protocol Set                             |
| QTc    | Corrected QT interval                        |
| QOL    | Quality of life                              |
| RECIST | Response evaluation criteria in solid tumors |
| SAEs   | Serious adverse events                       |
| SCLC   | Small cell lung cancer                       |
| SD     | Stable disease                               |
| SOP    | Standard operating procedure                 |
| SS     | Safety analysis set                          |
| SOC    | System organ class                           |
| TBIL   | Total bilirubin                              |
| TMB    | Tumor mutational burden                      |
| TR     | Thoracic radiotherapy                        |
| TKI    | Tyrosine kinase inhibitor                    |
| TEAEs  | Treatment-emergent AEs                       |
| ULN    | Upper limit of normal value                  |
| VALG   | Veterans Administration Lung Study Group     |
| WBC    | White blood cell count                       |
| WHO    | World Health Organization                    |

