## 7. Assessments

### Screening

- **Assessments within 14 days before study initiation:**
  - ✓ Sign the informed consent form;
  - ✓ Collection of medical history and baseline characteristics, including subjects' ID, gender, age,

- mailing address, and telephone;
- ✓ Collection of medical history (if the initial diagnosis is ES-SCLC, the time of initial diagnosis should be recorded; if the initial diagnosis is limited-stage SCLC and developed into ES-SCLC later, two of time points should be recorded; TNM staging), and smoking history;
  - ✓ Collection of previous anti-tumor therapies (e.g., the date and types of previous surgery; the start and end date of chemotherapy and radiotherapy, best response, treatment duration, and the date of the last dose);
  - ✓ Echocardiography;
  - ✓ Screening for infection, including human immunodeficiency virus (HIV) test, hepatitis B virus (HBV) test (if HBsAg is positive, quantitative serum HBV DNA levels will be detected), hepatitis C virus (HCV) antibody test (if HCV antibody is positive, quantitative HCV RNA levels will be detected);
  - ✓ Assessment of liver function;
  - ✓ Imaging examination (CT or MRI): PET will not be used as a routine method in the imaging assessment. Enhanced CT or MRI of the chest, abdomen, and pelvis is required for all subjects before administration. For subjects with bone metastases, a whole-body bone scan should be performed. All suspected lesions will be evaluated by imaging. During the screening period, a cranial plain scan plus enhanced MRI, and bone scan is required for all subjects (However, for subjects without bone metastases, whether the bone scan is performed will be decided by the investigator according to the symptoms);
  - ✓ Collection of archived or fresh tumor tissue samples;
  - ✓ Questionnaire for health-related quality of life (HRQOL);
  - ✓ Concomitant medications and adverse events.
  - **Assessments within 7 days before study initiation:**
    - ✓ Systematic physical examination: ECOG PS, height, weight, vital signs, and physical examination;
    - ✓ Serum pregnancy test: HCG testing (applicable to women of childbearing age);
    - ✓ Serum carcinoembryonic antigen (CEA) and neural-specific enolase (NSE);
    - ✓ 12-lead electrocardiogram;
    - ✓ Hemanalysis, urinalysis and stool analysis (including occult blood), thyroid function (T3, T4, FT3, FT4, TSH), coagulation function (PT, APTT, TT, FBG, D-Dimer, INR);

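### Section 3.5 prints the rule for maintenance after cranial irradiation in reverse, and its only timing item is a coronary-stent term, so no usable interval to restart is stated

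*Protocol*

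**What the plan says.** Section 3.5 of the protocol is headed as criteria for continuous treatment after PCI at the maintenance stage. The List of Abbreviations expands PCI as "Prophylactic cranial irradiation". The section's background text describes the course: "The dose of PCI was 25 Gy in 10 fractions over 2 weeks". It then allows PCI during maintenance and introduces a list of four items with "The maintenance therapy after the PCI is conducted unless meeting the following criteria". The items are:

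1. A condition opening "Subjects within 28 days after completing required tests and assessments in the screening period", under which the subject still satisfies the inclusion criteria and none of the exclusion criteria (first-line therapy excepted).
2. No antitumor treatment beyond study therapy and PCI.
3. "PCI with drug-eluting stents for 2 weeks".
4. "The review and approval by the principal investigator".

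The section closes with a sentence beginning "If subjects continue to receive the maintenance therapy after PCI", which says that such subjects are then followed according to the protocol.

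**The concern.** This is the protocol's only rule for going on with TQB2450 (an anti-PD-L1 antibody), anlotinib (an antiangiogenic kinase inhibitor) or their placebos after an irradiation that the protocol itself permits. It fails in two ways. Taken literally, the lead-in makes the listed items reasons not to give maintenance, when they read as requirements for giving it. And the item that should say when treatment may restart names a cardiac device, leaving a bare period of 2 weeks with no start or end point. At stake is whether sites apply one rule, at one time point, to patients who have just had cranial irradiation.

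**Working it through.** No figure in the plan rests on this rule, so there is nothing to recompute. The check sets the texts side by side.

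**Direction of the rule**

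| Text in section 3.5 | What it implies if the items are met |
|---|---|
| Heading | The list gives criteria for continuing |
| Lead-in as printed | Maintenance is not given |
| Item 1, still eligible | A reason to continue |
| Item 2, no outside antitumor treatment | A reason to continue |
| Item 4, investigator approval | A reason to continue |
| Closing sentence | Some subjects do continue after PCI |

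Every element except the lead-in points the same way. The lead-in is therefore the error: it should say *only if* where it says *unless*. It is a complete sentence in current body text, so a broken table, a redaction or an amendment log does not explain it.

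**The timing item**

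Given the protocol's definition of PCI, a drug-eluting stent cannot be part of the procedure. With those words removed, only 2 weeks is left. The same section uses 2 weeks for the length of the irradiation course, so the remnant could mean the course itself or a gap after it.

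**Search for the interval elsewhere**

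- Synopsis and section 5.2.1 (Stage 2): both permit PCI during maintenance, and neither gives a restart time.
- Section 3.5, background: about 3 weeks runs from chemoradiotherapy to the start of PCI, which is a different interval.
- Section 3.5, item 1: the 28 days is attached to screening assessments and not to irradiation. It also does not match the baseline windows in section 7, where one block is headed "Assessments within 14 days before study initiation" and the other is set at 7 days.
- Section 5.3.2: 12 weeks for TQB2450 and 8 weeks for anlotinib are maximum delays for adverse events, and the anlotinib limit excepts non-safety reasons.
- Section 7, End-of-treatment: records whether PCI was given and its dates.

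None of these states how long after cranial irradiation maintenance may restart.

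**Size**

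An estimate of patients affected would need PCI uptake. An estimate of the delay would need to know whether study drug is stopped during the course. The protocol gives neither, so neither quantity can be computed.

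**The case against.** The strongest reply is that this is a translation slip which misleads nobody. On direction, most of that stands. No site is likely to treat the principal investigator's approval as a reason to stop, and the heading and closing sentence make the intent clear. A reader might infer from the lead-in that eligible patients will actually be stopped and ineligible ones treated; the documents do not support that as a forecast of practice.

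On the interval, the reply has partial force. Item 1 re-applies the exclusion criteria, and exclusion criterion 2 asks for stable imaging at least 2 weeks after treatment of brain metastases, with steroids or anticonvulsants stopped for at least 14 days. That favours reading the remnant as a gap after the course. It does not settle the matter: the criterion concerns treated brain metastases, whereas section 3.5 describes PCI as given where there are none. It is also possible that item 1's 28 days was meant for repeat screening-type tests around PCI. The wording is too garbled to tell, and on that reading it still would not be an interval from the end of irradiation.

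On safety, item 4 is a real safeguard, and the adverse-event delay rules in section 5.3.2 continue to apply. No passage says that a short gap after cranial irradiation is hazardous, and section 8.3 allows limited palliative bone irradiation without naming any gap. A claim of demonstrated patient harm would go beyond the documents. What remains is that approval by an investigator does not tell that investigator which interval to apply.

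**Conclusion.** Wrong as written, and minor. The lead-in says the opposite of what the section intends, the timing item cannot be followed, and no other text fills the gap. Confidence in the wording error is high. That a gap of about 2 weeks after the course was intended is an inference.

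Two stronger readings should be resisted. A reader might put a range on the ambiguity, by counting 2 weeks from the start of irradiation under one reading and from its end under the other. That assumes study drug is held during the course. The protocol does not say so, and by allowing PCI during maintenance it leaves concurrent dosing open, so the documents do not bound the delay. A reader might also suspect the efficacy conclusion. Section 13.1 makes all randomized patients, analysed as randomized, the primary efficacy set, and nothing in section 3.5 touches the testing procedure. The intention-to-treat conclusion and the type I error are unaffected. The issue is consistent and safe conduct of treatment across sites.

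**What to change.** In section 3.5, change the lead-in so that maintenance after PCI *may be resumed only if all of the following are met*. Replace item 3 with the intended interval counted from completion of cranial irradiation. At least 2 weeks is the likely figure, but the sponsor must confirm it and should not have it assumed on its behalf.

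The cost is one protocol paragraph and a clarification letter to sites. No patients, visits or procedures are added.
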